### Sample Size

Prior studies have pilot-tested interventions to increase patient activation and found that PAM scores increased by a range of 4-8 points [
30,
31]. This difference was statistically significant, is thought to be clinically significant, and translates to a moderate effect size, Cohen’s
*d*=0.48. Given the repeated-measures design of the study, setting alpha = .05 and beta = .2, and using the effect size calculated from the literature, the required sample size will be n=36 patients. It is our goal to have 40 participants complete the PEP intervention.

In anticipation of significant participant dropout over the course of the study, we aimed to enroll 40 patients from Bellevue Hospital Center, 20 from Gouverneur Health, and 20 from Woodhull Medical Center. From these patients, it was our goal that 20 from Bellevue Hospital Center and 10 each from Gouverneur Health and Woodhull Medical Center would complete the PEP intervention. Because of these concerns about dropout, all participants who were randomized to the immediate intervention group but unable to attend the PEP intervention at that time were contacted for the T1 assessment with the deferred intervention group and invited back to attend the PEP intervention as part of that group (see
Figure 1).

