## Results

Recruitment for this study began in November 2014. As of June 2015, we met our enrollment goal of 80 patients. However, because of differences in site policies, the distribution of enrolled participants does not match our initial goals. By site, we have enrolled 40 participants from Bellevue Hospital Center, 31 from Gouverneur Health, and 9 from Woodhull Medical Center. As Woodhull Medical Center is located in a different part of New York City and serves a slightly different patient population, we plan to return to that site within the next few months to recruit an additional 11 patients.

Out of these 80 participants enrolled, the 71 from Bellevue Hospital Center and Gouverneur Health have been invited to attend the PEP intervention. Because of staff turnover and site-specific policies, we have as of yet been unable to hold any PEP intervention sessions at Woodhull Medical Center. Of the 71 participants invited to attend the PEP intervention, 45 have attended PEP session 1, 36 have attended the full PEP intervention, and 33 have returned for the post-PEP focus group. Of the 11 participants switched from the immediate intervention group to the deferred intervention group, 6 completed the T1 assessment and 3 attended at least one session of the PEP intervention. Coding and thematic analysis of the focus group discussions is not completed, but participants have reported that the PEP intervention was not only acceptable but a valuable experience that made them feel more empowered in their own health care. Several participants have even reported seeing their HCPs after completing the PEP intervention and changing their behaviors in the visit, which resulted in improvement in the quality of their visit.

Follow-up data collection is still underway and all patients who attended at least PEP session 1 will be called for all follow-up data points. Follow-up data collection is scheduled to conclude in April 2016 and the results of our data analysis are expected to be available by June 2016.

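### Moving immediate-arm non-attenders into the deferred group, and following up only session-1 attenders, means the immediate-versus-deferred comparison is no longer a randomised one

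*Protocol article*

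**What the plan says.** Under Recruitment, Randomization, and Retention, each cohort of 20 is split 10:10, which gives 40:40 for the 80 enrolled. The Methods overview times the deferred group's T1 to fall together with the immediate group's T3 and presents the waiting period as the control data.

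Under Sample Size, because dropout was expected, everyone randomised to immediate PEP who could not attend then was "contacted for the T1 assessment with the deferred intervention group and invited back to attend the PEP intervention as part of that group". Results confirms that this was done: "Of the 11 participants switched from the immediate intervention group to the deferred intervention group, 6 completed the T1 assessment". Three of the 11 went on to attend at least one session. Results also sets the follow-up rule: "all patients who attended at least PEP session 1 will be called for all follow-up data points".

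Data Analysis refers to the randomly determined groups only for the baseline comparison. The outcome analyses are run within each intervention group and then pooled, with T1 as the pre-PEP value for the deferred group. They end with mixed models that include group (immediate or deferred) and time. No outcome analysis is said to keep moved participants in the arm to which they were randomised.

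**The concern.** Group membership is changed after randomisation, and the reason for the change is non-attendance. Attendance at an empowerment course may well be related to patient activation, the primary outcome. The move takes non-attenders out of one arm and adds them to the other.

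The follow-up rule acts in the same direction. An immediate-arm participant who never came has no T3. A deferred participant gives T1 before anyone knows whether he or she will attend. Immediate T3 is therefore selected on attendance and deferred T1 is not.

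At stake is the only concurrent comparison of treated with untreated participants that the design offers. If the group label follows the move, that contrast can differ from zero with no PEP effect at all.

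**Working it through.** **The plan's own figure.** Inputs under Sample Size: d = 0.48, "setting alpha = .05 and beta = .2", a paired comparison (two-sided test assumed). The normal approximation gives ((1.960 + 0.842)/0.48)² = 34.07, so 35. The exact paired t-test has power 0.7996 at n = 36 and 0.811 at n = 37. The stated 36 is reproduced. It belongs to the within-person comparison, so the move does not change it.

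**Group sizes.** From 40:40, moving 11 leaves 40 − 11 = 29 immediate and makes 40 + 11 = 51 deferred. Moved share of the immediate arm: 11/40 = 27.5%. If only the 71 invited are counted and split evenly (assumed, 35.5 per arm), it is 11/35.5 = 31.0%. People randomised to deferred still make up 40/51 = 78.4% of the enlarged deferred group.

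**Spurious difference with no PEP effect.** Let N be the number per arm, f = 11/N, m the number of moved participants who contribute a T1, and delta the amount by which attenders exceed non-attenders. Let mu be the mean of a full randomised arm.

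- Immediate, attenders only: mu + f·delta. This excess is produced by the follow-up rule, with or without the move.
- Deferred after the move: mu − m(1 − f)·delta/(N + m). This deficit is produced by the move.

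| N | m | follow-up rule, f | move, m(1 − f)/(N + m) | sum |
|---|---|---|---|---|
| 40 | 6 | 0.275 | 6 × 0.725/46 = 0.095 | 0.370 |
| 35.5 | 6 | 0.310 | 6 × 0.690/41.5 = 0.100 | 0.410 |
| 40 | 11 | 0.275 | 11 × 0.725/51 = 0.156 | 0.431 |
| 35.5 | 11 | 0.310 | 11 × 0.690/46.5 = 0.163 | 0.473 |

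The rows with m = 6 fit the T1 data, since 6 moved participants completed it. The rows with m = 11 are an upper case. All rows take the 11 as the immediate arm's full set of non-attenders and assume that every truly deferred participant gave T1. With 40 such T1 values the 6 moved ones are 6/46 = 13% of the data; with 20 (assumed) they are 6/26 = 23%, and the part due to the move grows.

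**In PAM points.** Delta is not in the documents, so the values are assumptions. With m = 6, delta = 5 gives 0.370 × 5 = 1.9 to 0.410 × 5 = 2.1 points, and delta = 10 gives 3.7 to 4.1. With m = 11 the ranges are 2.2 to 2.4 and 4.3 to 4.7. For comparison, the earlier studies on which the sample size rests "found that PAM scores increased by a range of 4-8 points".

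**Effect on the type I error.** This takes 29 versus 51, all 11 counted and complete data. Assumed deltas of 0.2, 0.5 and 0.8 SD give spurious differences of 0.09, 0.22 and 0.35 SD. A nominal 5% test then rejects in about 7%, 15% and 32% of trials.

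**The case against.** Several points on the other side are sound.

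- A reader might infer that the trial now compares attenders with non-attenders. It does not. About 78% of the enlarged deferred group was randomised there, future attenders and non-attenders alike, and 3 of the 11 moved participants later attended. The contrast carries 37% to 47% of a full attender difference.
- A reader might blame the move for the whole distortion. The table shows that it accounts for about 0.09 to 0.16 delta; the larger part comes from calling attenders only. The move is also what produced a 3-4 month assessment for 6 people who would otherwise have none.
- Most planned tests are within-person. A stable difference in level cancels in a paired change, so the T0-T1 control change is biased only if non-attenders follow a different trend.
- T1 as the pre-PEP value for a moved participant who attends later is correct and is no part of this point.
- Non-attendance may be logistical. The article describes these people as unable to attend at the time and elsewhere mentions limited availability of staff and participants. Delta could be small, and a bias in favour of PEP is plausible but not shown.
- The article does not say which label the mixed models use, and an analysis plan may settle it.

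The last point does not remove the concern. The article states the reassignment itself, calls the participants switched, ties only the baseline check to the randomised groups, and gives T1 a place for the deferred group only. That is a rule already put into practice, not a detail left open. The follow-up restriction is stated outright and biases the concurrent contrast whichever label is used.

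**Conclusion.** The concern holds for the between-group comparison: immediate T3 against the coinciding deferred T1, and the group term in the mixed models if the text is followed as written. That comparison sets an attendance-selected immediate group against a deferred group mixed with immediate-arm non-attenders, and randomisation no longer protects it.

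The spurious difference in level is about 0.37 to 0.41 delta with the 6 moved participants who have T1, and 0.43 to 0.47 delta if all 11 are counted. This rests on an assumed delta of unknown sign, an assumed even split of the 71 invited where that base is used, and complete T1 data in the deferred arm. For an analysis of change from baseline, delta must be read as a difference in trend, which may be much smaller.

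The baseline comparison is as randomised and is not affected. The sample size of 36 stands, and the within-person pre-post comparisons are largely untouched. The documents do not support saying that the groups have become attenders versus non-attenders, or that the result is known to be biased towards PEP.

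**What to change.** 1. State that group means group as randomised in every between-group outcome analysis, including the mixed models.
2. Use the T1 assessments of the 6 moved participants as their immediate-arm outcomes at 3-4 months, since T1 was timed to coincide with T3.
3. Seek that one telephone questionnaire from every randomised participant, whether or not they attended, where the window is still open. The 9 people enrolled at Woodhull, where no sessions have been held, and the 11 still to be recruited there can be covered prospectively. Moved participants without T1 whose window has passed should be reported as missing.
4. Keep the switched grouping for pre-post or sensitivity analyses only, and label it as such.

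The cost is a few sentences and a small number of calls; some of the 5 missing T1 values will probably not be recovered. The statistical price is a diluted, as-offered estimate. If PEP acts only in those who attend and 29 of 40 did so, an effect of 4 to 8 points in attenders becomes 0.725 × 4 = 2.9 to 0.725 × 8 = 5.8 points. An attender analysis can be reported beside it as secondary.

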### Data Analysis

First, descriptive statistics including mean, standard deviation, range, skewness, and kurtosis for all continuous variables as well as frequencies for all categorical variables will be calculated at each time point (T0-T4). Because of concerns about the relatively small sample size and low literacy/health literacy, the normality of all continuous variables will be assessed both graphically with histograms as well as statistically using the Shapiro-Wilk and Kolmogorov-Smirnov tests, and transformations will be made if necessary. Then we will assess for any baseline (T0) differences between two separate groups: (1) the randomly determined immediate intervention and deferred intervention groups and (2) all participants who attended the PEP intervention and those who did not. Both of these analyses will be conducted using chi-square test for categorical variables and either independent samples
*t*test or Wilcoxon rank sum test for continuous variables.

Next, analyses will be conducted within each intervention group to evaluate for any effect of the PEP intervention on the primary, secondary, and exploratory outcomes using chi-square test for categorical variables (eg, PAM level, PCS) and either repeated-measures
*t*test or Wilcoxon signed rank test for continuous variables (eg, PAM score, AURA, Krantz, SF-12v2 Health Survey, DSMQ, and HbA
_1c_). Initial assessment (T0) will be compared with each of the post-PEP assessments (T2-T4) for each variable. For the deferred intervention group, initial assessment (T0) will be compared with the assessment at the end of the waiting period (T1), which will then be compared with each post-PEP assessment (T2-T4).

After analyzing each group individually, the groups will be combined in order to have a larger sample size for pre- and post-PEP comparisons. Pre-PEP intervention data for these analyses will consist of data from enrollment (T0) for participants in the immediate intervention group and data collected at the end of the waiting period (T1) for participants in the deferred intervention group. Repeated-measures analyses will be conducted on the primary, secondary, and exploratory outcomes as described above and pre-PEP data (either T0 or T1) will be compared with each post-PEP assessment (T2-T3).

Finally, multivariate analyses will be conducted using a series of generalized mixed-effects models to determine what effect patient characteristics, group membership, and time have on each continuous outcome measure. In each model, the dependent variable will be the outcome measure (eg, PAM, AURA, Krantz, SF-12v2 Health Survey, DSMQ, and HbA
_1c_). Independent variables will include participant characteristics such as age, sex, race/ethnicity, education level, annual income, number of years with T2DM, and health literacy as measured by the NVS. Other independent variables will include group (immediate vs deferred intervention) and time (T0-T4).

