## Methods

### Overview

The PEP is a randomized, wait-list control study (see
Multimedia Appendix 1) that aims to enhance general communication skills so that patients can participate in SDM during office visits, become activated in their own health care, and better manage their medical conditions.

Patients were recruited in cohorts of 20 and then randomly assigned to attend the PEP intervention immediately (immediate intervention) or after a waiting period (deferred intervention). All participants completed a baseline assessment at the time of enrollment (T0) and will complete follow-up assessments 1 week (T2), 3 months (T3), and 6 months (T4) after completion of the PEP intervention (see
Figure 1). Additionally, the deferred intervention group was assessed at the end of the waiting period (T1), immediately before being invited to attend the PEP intervention. The T1 assessment for the deferred intervention group was approximately 3-4 months after randomization and was timed to coincide with the T3 assessment of the immediate intervention group. A wait-list control design was chosen to create a control group with multiple time points of data collection (deferred intervention T0-T1) while still allowing for all participants who enrolled in the study to complete the PEP intervention and post-PEP follow-ups.

Aside from attending the PEP intervention, all participants continued to receive their usual care, including all scheduled primary care and specialty clinic appointments, HbA
_1c_monitoring, and all medications as directed by their physicians.

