### Recruitment, Randomization, and Retention

Research assistants (RAs) screened all of the clinic appointments each day to identify patients who were eligible for the study. Research assistants then briefly explained the study to all eligible patients who came to their appointment and obtained informed consent from those who decided to enroll (see
Figure 1). After obtaining informed consent, RAs read participants a set of questionnaires to complete the initial (T0) assessment (see
Table 1).

After 20 participants were enrolled in the study, a Web-based random number generator was used to generate a list of 20 integers between one and two. The list was refreshed until it contained 10 ones and 10 twos. Based on this list, participants were assigned in order of their study identification number to the immediate intervention (1) or deferred intervention (2) group. All participants in the immediate intervention group were contacted by phone to schedule the PEP intervention sessions and all participants in the deferred intervention group were contacted by phone and informed that they would be recontacted in 3-4 months to schedule their PEP intervention sessions.

Participants were compensated for participating in the study. They received US $10 and a MetroCard with US $10 at each of the two PEP intervention sessions. They also received US $60 and a MetroCard with US $10 for completing the study if they attended a post-PEP focus group.

In order to increase retention of deferred intervention participants, they received a letter from our program and an educational handout about T2DM in the mail approximately every 3 weeks. Handouts were sent in the same order and all handouts came from the Diabetes Care and Education website [
50]. In total there were four mailings: (1) Nutrition to Help Manage your Diabetes and Weight, (2) Eating Healthy on a Lean Budget, (3) Know Your Blood Sugar Numbers, and (4) Managing and Preventing Hypoglycemia. All four of these handouts were short, only 1-2 pages in length, and contained general information about T2DM that participants should have already obtained from their HCPs as part of their routine treatment. Therefore, we do not expect that receiving these handouts will cause a significant difference in the two randomized groups or otherwise affect the results of the study.

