#### Primary Outcome

The primary outcome of the study is patient activation, as measured by the short form of the PAM [
23]. The PAM is a 13-item interval level, unidimensional, Guttman-like scale with four response options, ranging from 1 = disagree strongly to 4 = agree strongly. It has been validated across multiple patient populations and has been shown to be reliable, with Rasch person reliability estimates ranging from .73-.84. The overall score on the PAM ranges from 0-100 and PAM scores can be categorized into four levels of activation. In level one, the lowest level, patients believe taking an active role in their health is important but are unprepared for this role. In level two, patients have some knowledge but still struggle to manage their medical conditions. In level three, patients begin to take action in terms of self-management but do not have the skills to support or sustain their behavior. Finally, in level four, patients have adopted self-management behaviors and work on maintaining them in stressful life situations [
23,
30].

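### The stated evaluation of PEP's effect is within-group and pooled pre-post testing; no between-arm contrast of immediate T3 with deferred T1 is specified

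*Protocol article*

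**What the plan says.** The Overview describes the design: "The PEP is a randomized, wait-list control study". It gives the reason for the wait-list: "A wait-list control design was chosen to create a control group with multiple time points of data collection", the control period being T0 to T1 in the deferred group. T1 falls about 3-4 months after randomisation and "was timed to coincide with the T3 assessment of the immediate intervention group". Allocation is balanced in blocks of 20 (Recruitment, Randomization, and Retention): "The list was refreshed until it contained 10 ones and 10 twos". The primary outcome is PAM: "The primary outcome of the study is patient activation, as measured by the short form of the PAM".

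Data Analysis compares the two randomised arms by a direct test only at T0. For efficacy, "analyses will be conducted within each intervention group to evaluate for any effect of the PEP intervention", using paired t or signed-rank tests for continuous outcomes. T0 is set against T2, T3 and T4; in the deferred group T0 is also set against T1, and T1 against T2 to T4. Next, "the groups will be combined in order to have a larger sample size for pre- and post-PEP comparisons", with T0 (immediate) or T1 (deferred) as the pre-PEP value, compared with T2 and T3. Last come mixed-effects models for each continuous outcome, with patient characteristics, group, and time (T0-T4) listed as independent variables.

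Sample Size bases n=36 on d=0.48 and the repeated-measures design.

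**The concern.** Objective 2 is causal: does PEP increase activation? The design supplies a concurrent control at 3-4 months, the only follow-up point at which one arm has been offered PEP and the other has not. The tests that carry the efficacy evaluation do not use it. A paired test cannot separate PEP from anything else that moves PAM over the same months: repeated administration of the questionnaires, continuing usual care, or the move to telephone for T3 and T4. Nor is a significant change in one arm alongside a non-significant change in the other a test of the difference between them.

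Several paired PAM tests are also planned and none is named as the deciding one, so the chance of a nominally significant result somewhere is well above 5%.

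**Working it through.** **1. The plan's own figure.** Inputs from Sample Size: d=0.48, alpha .05 (two-sided assumed, since sidedness is not stated), power 80%. For a single-group paired comparison, n = ((1.960 + 0.842)/0.48)² = 34.1, so 35 by the normal approximation. The exact paired t test has power 0.7996 at n=36. The stated 36 is reproduced, so the trial is sized for the pre-post comparison and not for the randomised one.

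**2. Does the mixed model supply the missing contrast?** I computed the expected coefficients of an additive group + visit model, omitting covariates and assuming an exchangeable correlation of 0.5.
- True PEP effect of 6 points in both arms, no time trend: the group coefficient is 0, and all 6 points fall on the T2, T3 and T4 terms.
- No PEP effect, drift of 1 point per month (assumed months from enrolment: immediate T2, T3, T4 at 0.5, 3.5, 6.5; deferred T1 to T4 at 3.5, 4, 7, 10): the T2, T3 and T4 terms are 2.25, 5.25 and 8.25, and the group term is -2.6.

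Both arms have had PEP by T2-T4, so the group main effect does not estimate the PEP effect. The time terms absorb drift. Immediate T3 and deferred T1 coincide in calendar time but carry different visit labels, so no single term isolates their difference.

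**3. Illustration: drift read as effect.** Sample Size cites PAM gains of 4-8 points and d=0.48. If d is the mean change over its SD, the SD of change is 4/0.48 = 8.3, 6/0.48 = 12.5 or 8/0.48 = 16.7. The drift is my assumption; the article gives none. With no PEP effect and the same mean drift in both arms, the two-sided rejection rate of the pooled paired t test at n=40 (the target number of completers), from the noncentral t with noncentrality (drift/SD)·√n, is:

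| Drift (points) | SD | Rejection rate |
|---|---|---|
| 1 | 12.5 | 8% |
| 2 | 12.5 | 17% |
| 3 | 12.5 | 32% |
| 4 | 12.5 | 51% |
| 3 | 16.7 | 20% |
| 3 | 8.3 | 60% |

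For one arm of 20 at SD 12.5, drifts of 2, 3 and 4 points give 10%, 17% and 27%.

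**4. Number of tests.** PAM-score tests: immediate 3; deferred 3 + 1 + 3 = 7; pooled 2; total 12. If the deferred group is read as having only T0-T1 and then T1 against T2-T4, its count is 4 and the total is 9. T0-T1 does not test PEP; without it the totals are 11 and 8. I simulated 100,000 trials with no drift, no PEP effect, 20 per arm and an assumed between-visit correlation of 0.6. The chance of at least one p<.05 was 36% (12 tests), 34% (11), 29% (9) and 26% (8). Correlations of 0.4 and 0.8 changed this by less than one point.

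**5. Power of the randomised contrast.** Apply d=0.48 to the between-arm difference in SD units of the PAM score (an assumption). Per arm, n = 2 × 34.07 = 68.1, so 69, or 70 by the t test. For ANCOVA the residual SD is multiplied by √(1-r²); r is not in the article. t-based power:

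| Analysis | 40 per arm | 20 per arm |
|---|---|---|
| Unadjusted | 56% | 32% |
| ANCOVA, r=0.5 | 69% | 40% |
| ANCOVA, r=0.7 | 84% | 54% |

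Forty per arm means all 80 enrolled contribute, which is the ceiling. Twenty per arm is the 40 target completers split evenly.

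**The case against.** A reader might infer that the randomised arms are never compared after baseline. The article does not support that: group is in a stated model of every continuous outcome, PAM included, and an interaction or contrast is detail that a journal article may leave to a fuller analysis plan. What stands is narrower. No between-arm contrast is specified, the model as listed does not contain one, and the article itself assigns the evaluation of PEP's effect to the within-group tests. A fuller plan would have to displace that statement, not merely add to it.

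The control period is also not ignored. The deferred T0-T1 test shows drift in that arm, and the pooled analysis takes T1 as that arm's starting value, so change during waiting is not credited to PEP there. It would be wrong to say that all change over time counts as PEP effect. But the T0-T1 test sits in one arm and is not set against the immediate arm, whose T0-to-T3 change spans the same months with no correction.

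One might add regression to the mean from selecting on HbA1c. Patients were selected on HbA1c, within a range bounded on both sides, and not on PAM. That argument concerns the exploratory HbA1c outcome and is not made here for PAM. The move to telephone is softened, though not removed, by research assistants reading every questionnaire aloud under a standardised protocol.

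The rejection rates depend on an assumed drift and SD and show what could happen, not what will.

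**Conclusion.** The point holds in this form: the plan builds a concurrent randomised control and then rests its conclusion about PEP on uncontrolled pre-post tests, with a mixed model that does not recover the randomised contrast. Time-related change in PAM can be reported as a PEP effect. The size depends on a drift that the article does not give: near the nominal level for a small drift (8% at 1 point, SD 12.5), and 20% to 60% for 3 points over the SD range implied by the cited gains. Separately, with no drift, the absence of a named deciding test leaves roughly a 26% to 36% chance of at least one nominally significant PAM result. The reasoning from the text does not depend on these assumptions. It should be corrected before the outcome data are analysed; follow-up was still under way when the article was written.

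**What to change.** Name one primary analysis: PAM score at 3-4 months after randomisation, immediate T3 versus deferred T1, compared between arms as randomised and adjusted for T0 PAM, at two-sided alpha .05. ANCOVA, or a constrained longitudinal model with time aligned to the calendar rather than the visit label, would serve. Analyse secondary outcomes the same way. Label the within-group and pooled pre-post tests descriptive, and say that they do not support a claim of effect.

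Keep the 11 participants who were switched to the deferred group in the immediate arm, using their T1 assessment as the 3-4 month value, and state the assumption under which remaining missing values are handled.

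This is more than a change of wording. According to Results, follow-up calls go to those who attended at least session 1, and only 6 of the 11 switched participants completed T1, so 3-4 month data for immediate-arm non-attenders will be incomplete. Power also falls below the 80% stated for the pre-post comparison, to the values in the second table of the working. The plan should state the power of the randomised comparison and report its interval on that footing.

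### The primary outcome (PAM) has no primary time point or decisive comparison, so at least 8 unranked pre-post tests of the PAM score stand beside a sample size that fits one

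*Protocol article*

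**What the plan says.** The Primary Outcome section identifies the endpoint by instrument: "The primary outcome of the study is patient activation, as measured by the short form of the PAM". It adds that "The overall score on the PAM ranges from 0-100 and PAM scores can be categorized into four levels of activation". It gives no assessment time and no comparison.

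The Sample Size section takes a 4-8 point rise in PAM score from earlier studies, converts it to d = 0.48, and works with "setting alpha = .05 and beta = .2". It concludes that "the required sample size will be n=36 patients. It is our goal to have 40 participants complete the PEP intervention".

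The Data Analysis section then evaluates the effect of PEP on the outcomes in three settings:
- **Immediate group:** "Initial assessment (T0) will be compared with each of the post-PEP assessments (T2-T4) for each variable".
- **Deferred group:** T0 against T1, then T1 against each of T2, T3 and T4.
- **Combined groups:** pre-PEP (T0 for immediate, T1 for deferred) against T2 and T3. The stated reason for combining is a larger sample.

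PAM score is tested by a paired t or Wilcoxon signed rank test. PAM level is among the outcomes given a "chi-square test for categorical variables (eg, PAM level, PCS"). A series of mixed-effects models with group and time closes the section. No analysis is called primary.

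**The concern.** A primary outcome is only fixed once the measure, the time and the comparison are all stated. Here the measure is named and the other two are open. Each pre-post PAM test addresses the same question, whether PEP raises activation, and the article does not say which one answers it.

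The time points are not interchangeable. T2 comes one week after the sessions and is collected at the start of the focus group where possible. T3 and T4 are telephone assessments at 3 and 6 months. A rise at one week that has gone by three months is a different finding from a lasting one, yet the plan gives both the same standing. The section is also uneven: within-group tests run to T4, while the combined tests stop at T3.

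At stake is how far a statement that PEP increased activation can be trusted, given that the sample was sized for one test.

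**Working it through.** **1. Reproduce the sample size.** Inputs from the Sample Size section: d = 0.48, alpha .05, power .80. Sidedness is not stated; two-sided is assumed. Treat d as the standardized within-person change in one paired test.
- Normal approximation: ((1.960 + 0.842)/0.48)² = 34.1, so 35.
- Noncentral t: 37, with power 0.7996 at n = 36 and 0.841 at n = 40.
- Alternatives do not match: one-sided gives 27 (normal) or 29 (t); a two-arm comparison needs 69 per arm.

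The stated 36 is therefore one two-sided paired test on the PAM score. The goal of 40 completers is a total across both groups, so the matching analysis is the combined one. A single group of 18-20 would have power of only 48-53%.

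**2. Count the tests of a PEP effect on the PAM score.**
- Immediate: T0 against T2, T3, T4 = 3
- Deferred: T1 against T2, T3, T4 = 3
- Combined: pre-PEP against T2, T3 = 2
- Total 3 + 3 + 2 = 8

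The waiting-period test (T0 against T1) would make 9. If T0 is also compared with T2-T4 in the deferred group, the count is 12. The same 8 comparisons on PAM level would bring 8 to 16.

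**3. Chance of at least one p<.05 when nothing changes.** Independent tests give an upper reference, 1 − 0.95^k:
- k = 2: 1 − 0.95² = 9.75%
- k = 8: 1 − 0.95⁸ = 33.7%

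The tests share baselines and participants, so they are correlated. Paired t tests were simulated under no change, 20,000 trials per scenario. The assumptions were 18-20 completers per arm and exchangeable or AR(1) within-person correlation of 0.5-0.7; a second run used 20 per arm and equal correlation of 0.3-0.9.
- Two combined-group tests: about 9%
- Three tests within one group (second run): about 13%
- All 8 score tests: 24-27% for any p<.05; 12-14% for any favourable result, against 2.5% for one test
- All 8 score tests plus 8 level tests: about 36-38% (illustrative: equally likely levels, correlation 0.3-0.5)

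**4. What keeping several tests would cost.** With a Bonferroni split at d = 0.48:
- Two tests (alpha .025): n = 44; power at n = 36 is 70%.
- Eight tests (alpha .05/8 = .00625): n = 60; power is about 50% at n = 36 and 56% at n = 40.

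**5. Whether naming form and time alone is enough.** If only PAM score at T3 were named, T3 would still be tested in the immediate, deferred and combined groups. Simulated on the same basis, the chance of any p<.05 is about 11-12%. The group and the test must be named too.

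**The case against.** Several points on the other side stand.

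- **Form.** A reader might infer that score and level are equally open as the primary form. The documents do not support that. The sample size is in PAM points, the Primary Outcome section treats the score as the measure from which levels are derived, and the mixed models take PAM as continuous. What remains is that Data Analysis also tests PAM level and does not call it supportive.
- **Size.** Counting all 8 tests is the harshest reading. The within-arm tests have about half the powered sample, and the combined analysis has only two PAM-score tests. On that reading the figure is about 9%. The 24-27% also includes results unfavourable to PEP.
- **Alpha.** A reader might infer that the trial breaks a promised 5% error rate. The article makes no such promise; .05 appears only as a sample-size input. Nor does it say that any significant PAM test may be claimed as success.
- **Unseen documents.** A multiplicity rule and a ranking of analyses may sit in an analysis plan not shown. The primary time point and comparison, however, are protocol content. The article has dedicated sections on the outcome and the analysis, and these set out parallel tests without an order.
- **Mixed model.** It could be the decisive analysis, but it is not so designated, and n = 36 does not correspond to it.

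**Conclusion.** The point holds as a gap in time point and decisive comparison. As written, the plan runs at least 8 unranked tests of a PEP effect on the PAM score, while its sample size reproduces as one paired test. The sample-size arithmetic is not at fault.

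The excess is modest on the most favourable reading (about 9% for the two combined-group tests) and substantial if every score test counts (about 24-27%, or 12-14% favourable). These figures rest on assumed group sizes and correlations, a two-sided .05 for each test, and no change over time without PEP. They varied little across the correlations tried.

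The change should be made, but this does not invalidate the design.

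**What to change.** Before the outcome data are analysed, state one primary endpoint and one primary test. For example: the change in PAM score (0-100) from pre-PEP (T0 for immediate, T1 for deferred, as Data Analysis already defines it) to T3 in the combined group, tested once at two-sided .05. This is the comparison that n = 36 supports, with power of about 80%, or 84% at 40 completers.

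The reason for T3 is that it is the later of the two combined-group time points and reflects sustained rather than one-week change. The Overview notes that the deferred T1 "was timed to coincide with the T3 assessment of the immediate intervention group", but that alignment helps a comparison between arms and is no argument for a pre-post change.

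Label PAM score at T2 and T4, the within-arm tests, PAM level and the mixed model as secondary or supportive.

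The cost is a short addition to the protocol and no new data. A T2-only, single-arm or level-only result could no longer be reported as primary success. The Results section says that 33 participants had already returned for the focus group, where T2 is collected if they attend. The choice should therefore be documented as made during data collection but before analysis.
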